#### Pre-ulcerative lesions and ulcers

2.6.1

The assessment of pre-ulcerative lesions (hyperkeratosis) and ulcers will be performed according to the study by Colagiuri et al. [42], in which pre-ulcerative lesions and ulcers were evaluated using six grades, as follows (Fig. 4):1.Grade 1: minimal thickening of the keratin layer2.Grade 2: moderate thickening of the keratin layer3.Grade 3: marked thickening of the keratin layer4.Grade 4: callus with subcutaneous bleeding5.Grade 5: callus with ulcer6.Grade 6: callus with infected ulcer

**Fig. 4 fig4:**
[figure not shown]
Grades 1 to 6 of severity of pre-ulcerative lesions and ulcers.

Grades 1 to 4 refer to pre-ulcerative lesions, while Grades 5 and 6 are already established ulcers. If the participant is classified as Grade 5 or 6 at baseline assessment, they will not be included in the study but may be included later after the ulcer has healed.

#### Plantar pressure distribution during gait

2.6.2

A pressure platform (emed-q100; novel, Munich, Germany) will be used to assess pressure distribution during walking. Data will be collected at 100 Hz. Patients will walk through a 5 m walkway in a self-selected and comfortable speed and the platform will be placed close to the end of the walkway, allowing patients to perform 2–3 steps before stepping onto the plate and 1–2 steps after the plate. Immediately before data collection, participants will be instructed to carry out a habituation period to feel comfortable to the environment and to the pressure plate. The walking speed will be recorded (chronometer) and the same speed will be kept in all follow up assessments. At T3 and T6, IG participants will be assessed with socks with and without orthoses. The procedure will be repeated up to three steps on each side. For analysis of the regions of interest, a geometric mask that divides the foot into seven regions—rearfoot, midfoot, medial forefoot, central forefoot, lateral forefoot, toes, and hallux—will be used [43]. Peak pressure, contact area, and pressure–time integral in each sub-plantar area will be analyzed.

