### Trial design and setting

2.1

This will be a superiority controlled clinical parallel trial with random allocation and single-blind assessment. The trial has been approved by the Research Ethics Committee of the School of Medicine at USP (CAAE 65204622.4.0000.0068, 11/24/2022) and registered with ClinicalTrials.gov (NCT05683106, 12/20/2022). Any important protocol modifications will be reported to the relevant parties (funding sources and trial registration). This trial will have an allocation ratio of 1:1 and will follow all SPIRIT recommendations [40]. Fig. 1 presents a flowchart with the steps for the clinical trial.

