#### Intervention group

2.4.2

IG participants will receive the same instructions as the CG participants in addition to customized silicone orthoses for toe realignment according to their needs. When not using therapeutic footwear, common footwear will be accepted if it provides adequate fit to accommodate the orthoses comfortably in order to avoid possible trauma resulting from improperly sized footwear.

During the reassessments, IG participants will have their orthoses examined and repaired or replaced if necessary. The criteria for discontinuing orthosis use during the study will include moderate to severe pain or any other condition that exposes the participant to discomfort, trauma caused by the use of the orthoses, allergy to the orthosis material, difficulty adapting to the orthoses, and imbalance. Participants will be instructed to promptly report any type of adverse events or discomfort. The criterion for discontinuing the intervention will also include the participant's own withdrawal from the study. If the IG participant stops using the orthoses without any explanation, their participation in the study will be terminated and they will be considered a drop out.

A bunion (or hallux valgus) will be treated with a toe separator type of orthosis to realign the toe (Fig. 2A). For flexible claw toes, a subphalangeal orthosis will be provided for realignment (Fig. 2B). A flexible hammer toe will be treated with an omega-type orthosis that protects the back of the toe without covering the nail, anchoring the support points in the plantar region of the toes (Fig. 2C). Prominences of the metatarsal heads will be treated with a semi-rigid silicone metatarsal head protector orthotic, and in the areas where impact needs to be cushioned, extra soft silicone will be used (Fig. 2D).

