**Fig. 2 fig2:**
[figure not shown]
**–** Toe orthosis types: (A) toe separator-type orthosis, (B) subphalangeal orthosis for flexible claw toe, (C) omega-type orthosis, (D) orthosis for protection of the metatarsal heads.

To prevent adverse effects, IG participants will received orthosis guidance, such as cleaning the orthoses and interdigital spaces with soap and water, adequately drying the toes and interdigital region, using talcum powder to absorb moisture between the toes, always using the orthoses with appropriate footwear and with socks to promote sweat absorption and prevent orthosis displacement, using the orthoses during all day, except during bath and when sleeping, and monitoring the integrity of the orthoses and always reporting any changes in the feet or orthoses.

Throughout the study, possible adverse effects will be evaluated, such as skin irritation (redness, itching, contact dermatitis, or erosions), discomfort or pain sensation (bulky orthoses), muscle contractions, hyperkeratosis, increased foot sweating, or trauma from friction (caused by an orthosis that has folded or is poorly adjusted to the toes). Adherence to the intervention will be evaluated through scheduled reassessments every 3 months and weekly via WhatsApp messages.

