### Outcome assessments and timeline

2.5

Two researchers blinded to group allocation will perform the baseline and all follow-up assessments. IG participants will be assessed at baseline, after 7 days (via a telephone questionnaire about safety and comfort), at 3 months, and at 6 months. CG participants will be assessed at baseline and 3 and 6 months. Intervals of 3 and 6 months were established for the reassessments following the IWGDF guidelines, which recommend that individuals with DM classified as risk 2 need to be evaluated every 3–6 months and with risk 3 every 1–3 months. Table 1 presents the primary and secondary outcomes and the study period in which they will be evaluated according to the SPIRIT guidelines [40].

**Table 1 tbl1:** Primary and secondary outcomes of the study following the SPIRIT guidelines.

Outcomes		When participants will be assessed			
Primary	Measures	Baseline	7 days	3 m	6 m
Pre-ulcerative lesions and ulcers	Assessed according Colagiuri et al. (1995), which classifies hyperkeratosis into 6 grades.	**X**		**X**	**X**
**Secondary**	**Measures**				
Plantar pressure distribution during gait	Pressure peak, pressure-time integral, contact area by anatomical masking	**X**		**X**	**X**
Range of motion (ROM) of metatarsofalgeal joint	To assess ROM, a manual goniometer will be used to assess joint amplitude passively and actively	**X**		**X**	**X**
Toes alignment and flexibility	To measure toes alignment, toes will be photographed with markings on the metatarsophalangeal and interphalangeal joints.	**X**			**X**
Foot health and functionality	FHSQ-BR Domain scores	**X**		**X**	**X**
Quality of life	EQ-5D questionnaire	**X**		**X**	**X**
Satisfaction and safety	Satisfaction and Safety Questionnaires		**X**	**X**	**X**
Comfort	Analog numerical comfort scale		**X**	**X**	**X**

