### Primary and secondary outcomes

2.6

The incidence of ulcers and pre-ulcerative lesions will be considered the primary outcomes. The plantar pressure distribution during walking, metatarsophalangeal joint range of motion (ROM), toe alignment, foot function, overall foot health, quality of life, satisfaction, safety, and comfort will be secondary outcomes.

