#### Satisfaction and safety

2.6.4

To evaluate the safety and satisfaction with the use of orthoses, a structured closed questionnaire will be applied consisting of 11 questions related to safety and seven related to satisfaction. Responses will be assessed using a 5-point Likert scale (1 = completely disagree; 2 = disagree; 3 = neither agree nor disagree; 4 = agree; 5 = completely agree). The questionnaire will be administered by phone one week after baseline and repeated at 3 and 6 months from baseline.

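### The assessors called blinded also run the orthosis-on walking trials, so single-blind assessment does not hold, as written, for the visually graded primary outcome

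*Protocol article*

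**What the plan says.** Section 2.1 describes a "superiority controlled clinical parallel trial with random allocation and single-blind assessment". Section 2.3 explains that neither the nurse who makes the orthoses nor the participants can be masked, so the label refers to the assessors. Section 2.5 says who they are: "Two researchers blinded to group allocation will perform the baseline and all follow-up assessments". Section 2.8 also describes those acquiring the data as blinded to allocation.

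The outcome they grade is primary. Section 2.6: "The incidence of ulcers and pre-ulcerative lesions will be considered the primary outcomes". Section 2.6.1 uses a six-grade visual scale whose lower steps are verbal, for example "Grade 2: moderate thickening of the keratin layer".

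For plantar pressure, Section 2.6.2 states: "At T3 and T6, IG participants will be assessed with socks with and without orthoses". For the questionnaires, Section 2.6.4 states: "To evaluate the safety and satisfaction with the use of orthoses, a structured closed questionnaire will be applied". Section 2.6.5 adds a comfort scale about wearing the orthoses. Table 1 schedules lesion grading, plantar pressure, satisfaction and safety, and comfort all at 3 and 6 months.

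The one masking safeguard stated for the visits is in Section 2.3: participants are told not to disclose their group.

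**The concern.** The article asserts a property, blinded assessment at every follow-up, that its own procedures remove. A walk with the orthosis on exists only in the IG. Running it discloses the arm whatever the participant says, and silence does not hide a device that is part of the test.

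Lesion grading is where this matters most. Grades 1 to 3 separate minimal, moderate and marked thickening by eye, and the article gives no measured cut-off. With participants and the treating nurse unmasked, masking of the grader is what protects the primary outcome from detection bias. The blinded tabulation and analysis described in Section 2.3 cannot correct a grade that was recorded with knowledge of the arm.

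**Working it through.** The plan states no figure on this point, so the check is a cross-reading, followed by an illustration of sensitivity.

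**Cross-reading**

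1. Who does the follow-up work: the two blinded researchers, for all of it (Section 2.5), with blinded data acquisition repeated in Section 2.8.
2. What the work includes at 3 and 6 months (Table 1): lesion grade, plantar pressure, satisfaction and safety, comfort.
3. What reveals the arm: the with-and-without-orthosis walks, which are expressly for the IG (Section 2.6.2). The questionnaires point the same way by content, since they ask about using and wearing orthoses.
4. Steps 1 to 3 together: someone in the blinded pair sees the orthosis at 3 months. Nothing in the article keeps that person away from lesion grading.
5. Does order within a visit help? If lesions are graded before the walking trials, the 3-month grade can be protected from that visit's trials. The 6-month grade cannot, because an assessor who ran the 3-month trials already knows the arm. Only a different grader solves this.
6. Could exposure come earlier? Section 2.5 lists a 7-day telephone contact for the IG only. If the same two researchers make that call, exposure precedes the 3-month visit. The article does not say who calls, so 3 months is the latest point, not necessarily the first.
7. Is masked grading described elsewhere? Photographs are planned only for toe alignment (Section 2.6.3), not for lesions.

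**Illustration of sensitivity (assumed inputs)**

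- Per arm n = 54/2 = 27, from the total of 54 in Section 2.7.
- Test: Pearson chi-squared without continuity correction, two-sided 5%, as used for the sample size.
- Assumed: no true effect; control lesion risk p of 0.745 or 0.60; a fraction m of IG positives recorded as negative. The article gives neither p nor m.
- Observed IG risk = p(1 − m). For p = 0.745: 0.6705, 0.596 and 0.5215 at m = 0.10, 0.20 and 0.30. For p = 0.60: 0.54, 0.48 and 0.42.
- X² = [(x_C − x_I)/n]² / [p̄(1 − p̄)(2/n)], with p̄ = (x_C + x_I)/(2n). The probability that X² exceeds 3.84 is summed over all pairs of binomial counts.

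| p | m = 0 | m = 0.10 | m = 0.20 | m = 0.30 |
|---|---|---|---|---|
| 0.745 | 0.056 | 0.099 | 0.220 | 0.400 |
| 0.60 | 0.047 | 0.065 | 0.128 | 0.239 |

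With m above zero, nearly all rejections favour the IG. The table shows how the test would react to a given bias. It is no estimate of the bias.

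**The case against.** The strongest defence is that a journal article condenses the protocol. It does not say that both assessors do every task, and a division of work may exist in the full document. That is fair as far as silence goes. But the article is not silent here: it assigns all follow-up assessments to blinded people and prescribes an IG-only test with the device. An unwritten split might rescue the practice, but not the claim as worded, since whoever runs those trials is not blinded.

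Several stronger readings are tempting and are not supported:

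- **That the assessors also inspect and repair orthoses.** Section 2.4.2 says "During the reassessments, IG participants will have their orthoses examined and repaired or replaced if necessary" but not by whom, and Section 2.3 mentions an unblinded nurse who makes them.
- **That the later questionnaires are expressly IG-only and given by the graders.** IG-only follows from their content and from the IG-only 7-day call; the article does not name the person who administers them.
- **That weekly messages prompt lesion reports unequally.** Section 2.4.2 says "Adherence to the intervention will be evaluated through scheduled reassessments every 3 months and weekly via WhatsApp messages". That describes an adherence check. Sections 2.4 and 2.9 ask patients in general, not only the IG, to report foot problems, and Table 1 schedules primary grading only at baseline, 3 and 6 months.
- **That the table in the working measures the damage.** Section 2.6.1 counts grades 1 to 4 all as pre-ulcerative lesions, so moving a foot from marked to minimal leaves it positive. The table needs a callus to be recorded as none, a larger error. It also uses the chi-squared test, whereas Section 2.7 names a repeated-measures ANOVA for the analysis.

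**Conclusion.** The contradiction holds. As written, Sections 2.5 and 2.8 cannot be satisfied together with Section 2.6.2. A lesion grader learns the allocation by the 3-month visit at the latest, and the 6-month grade is exposed whatever the order of tasks within a visit. The single-blind claim therefore fails for a primary outcome judged by eye.

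This conclusion rests on taking the Section 2.5 assignment at its word. It needs no assumption about who inspects orthoses or who sends messages, and it does not depend on the illustrative figures. The amount of bias, if any, cannot be determined from the article. Confidence is high for the conflict between the sections and does not extend to any particular size of effect. The point should be corrected, and because recruitment is open (Section 3.1), a correction can still protect visits yet to come.

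**What to change.** Divide the tasks between the two existing assessors and say so in Section 2.5.

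- **Assessor A** grades calluses and ulcers at every visit, with orthoses removed and out of sight beforehand, and takes no part in any orthosis-related measure at any time in the study.
- **Assessor B** runs the pressure trials and the orthosis questionnaires and is described as unblinded.
- Align Sections 2.1 and 2.8 so that blinding is claimed for lesion grading and not for all data acquisition.

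If the split cannot be made, drop the blinded-assessor claim for follow-up and report the lesion grading as unblinded.

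Cost: changes to wording and visit flow, with no extra staff. The downside is that pressure and questionnaire outcomes are openly reported as unblinded and that each assessor's role is fixed, so the two can no longer stand in for each other.

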#### ROM of the metatarsophalangeal joint and toe alignment and flexibility

2.6.3

To assess ROM, a manual goniometer will be used to passively and actively measure joint amplitude [44]. To measure toe alignment, toes will be photographed with markings on the metatarsophalangeal and interphalangeal joints at baseline and 6 months, and the alignment will be qualitatively evaluated.

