## Discussion

3

This paper describes a randomized trial protocol that aims to evaluate the efficacy and safety of customized silicone digital orthoses in preventing ulcers, pre-ulcerative lesions, and peak pressures during gait in people with DPN and risk category 2 or 3. This study is supported by evidence that people with DPN often develop calluses due to toe misalignment and increased plantar pressure. If toe deformities and calluses are not addressed in a timely manner, they can evolve into plantar ulcerations [25,33,48]. Once installed, these ulcerations are difficult to manage and have the potential for amputation. Therefore, early prevention and treatment are crucial.

Conservative treatment for dealing with calluses, including debridement, is the first clinical choice; however, when that fails, surgical treatment is the alternative [49]. Although conservative treatment provides quick relief for patients, it is of limited benefit because if plantar pressure at the forefoot is not redistributed effectively, the callus will soon form again as a way of protecting against chronic excessive mechanical stimulation [50]. Therefore, callus removal must be accompanied by strategies for redistributing plantar pressure. Customized silicone orthoses are a strategy for toe realignment and, consequently, plantar pressure redistribution. A single clinical trial has indicated the efficacy and safety of using customized orthoses at the forefoot to reduce the incidence of pre-ulceration lesions in people with DPN [35]. In addition, other studies have evaluated the use of silicone orthoses aimed at reducing peak pressure with promising results [[36], [37], [38]]. Although the use of silicone orthoses is recommended by the IWGDF guidelines [32], its use worldwide is limited due to a lack of evidence. Thus, a randomized controlled trial addressing the effectiveness of this approach to prevent ulcerations and pre-ulcerative lesions would provide more consistent evidence for the adoption (or not) of this approach as a preventive strategy for people with DPN.

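### Toe realignment, the first step of the orthosis's stated mechanism, has no quantitative endpoint, although joint-marked photographs are already planned

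*Protocol article*

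**What the plan says.** Section 2.6 lists toe alignment among the secondary outcomes: "The plantar pressure distribution during walking, metatarsophalangeal joint range of motion (ROM), toe alignment, foot function, overall foot health". Flexibility does not appear in that list.

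Section 2.6.3 gives the procedure: "toes will be photographed with markings on the metatarsophalangeal and interphalangeal joints at baseline and 6 months, and the alignment will be qualitatively evaluated". Table 1 in section 2.5 names the outcome as alignment and flexibility together, schedules it at baseline and 6 months, and gives one measure: "To measure toes alignment, toes will be photographed with markings on the metatarsophalangeal and interphalangeal joints". Range of motion of the metatarsophalangeal joint is a separate row of Table 1, taken at baseline, 3 and 6 months. For it, section 2.6.3 says: "To assess ROM, a manual goniometer will be used to passively and actively measure joint amplitude".

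The Discussion states the mechanism: "Customized silicone orthoses are a strategy for toe realignment and, consequently, plantar pressure redistribution". Section 2.4.2 likewise describes the orthoses as given for realignment of the toes.

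The pressure step is quantified in section 2.6.2: "Peak pressure, contact area, and pressure–time integral in each sub-plantar area will be analyzed". For the intervention group (IG) it adds: "At T3 and T6, IG participants will be assessed with socks with and without orthoses".

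Section 2.7 describes one inferential analysis: a two-way repeated measures ANOVA with group, time (baseline, 3 and 6 months) and interaction effects. The intervention effect is to be described by Cohen's d and by differences between means with 95 % confidence intervals.

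**The concern.** The argument for the device has three links: the toes are realigned, pressure is redistributed, and fewer lesions form. The second and third links have defined measurements. The first has a photograph and an unscaled judgement, even though the section speaks of measuring and the joints are to be marked.

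At stake is how the result can be explained. Suppose pressure and lesions do not differ between arms. The trial would then have no number to show whether the toes failed to realign or realigned without unloading the forefoot. Suppose instead that pressure does fall. Section 2.4.2 includes a metatarsal head protector with softer silicone for cushioning, so a fall in pressure need not have come through realignment.

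There is also a smaller inconsistency. Flexibility is in the section 2.6.3 heading and in the Table 1 outcome name, is absent from the section 2.6 list, and has no measure labelled as its own.

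**Working it through.** The point rests on no figure in the plan, so there is none to reproduce. The check sets the sections side by side.

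**1. Each link and its measurement**

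| Link in the stated mechanism | Measurement | Visits | Numeric? |
|---|---|---|---|
| Toe realignment | Joint-marked photographs, judged qualitatively (2.6.3, Table 1) | Baseline, 6 months | No |
| Pressure redistribution | Peak pressure, contact area and pressure–time integral in seven foot regions; in the IG with and without orthoses at 3 and 6 months (2.6.2) | Baseline, 3, 6 months | Yes |
| Lesions and ulcers | Six-grade classification (2.6.1) | Baseline, 3, 6 months | Graded |

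Only the first row lacks a number or a defined grade.

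**2. Does the outcome fit the analysis?** A difference between means is (IG mean) − (control mean), and Cohen's d is that difference divided by a standard deviation. Both need a numeric value per participant, and section 2.6.3 produces none. The ANOVA is also set out for three times, while alignment is taken at two.

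**3. Does another measurement stand in for alignment?**
- *Goniometry.* Range of motion says how far a joint can move, not where the toe rests. The section heading and Table 1 limit it to the metatarsophalangeal joint, while the photographs also mark the interphalangeal joints.
- *Pressure.* This is the consequence of realignment in the stated chain. It can also change through cushioning, so it does not identify realignment.

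**4. Could the planned photographs give an angle?** The section's own aim is stated as "To measure toe alignment, toes will be photographed with markings on the metatarsophalangeal and interphalangeal joints". Lines through marked joints define angles, so it is a reasonable inference that they can be read. The article does not give the camera view, the calibration, or whether the orthosis is worn in the picture.

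**5. Workload.** At most 60 participants × 2 visits = 120 photograph sets. With the 10 % loss assumed in section 2.7, 60 × 0.90 = 54 at 6 months, so about 60 + 54 = 114.

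**The case against.** The strongest reply is that the mechanism is measured where it matters most. Pressure is quantified by region, including the toes and hallux, and in the IG with and without the device. A reader might infer from the qualitative photographs that the mechanism cannot be tested at all. The documents do not support that: the pressure link is testable, and the pressure data will show whether offloading occurred. What is missing is a quantitative test of realignment alone.

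Second, a qualitative reading could be recorded in categories and compared between arms, and a rating rule may sit in a fuller document that is not shown. This stands in part. Absence of a rating rule from an article would be no finding. But the article goes further and fixes a qualitative judgement. A rating rule could make that comparable, but would not turn it into a measured angle.

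Third, a reader might suspect expectation bias in an unscaled judgement. Section 2.5 has two researchers blinded to allocation making all assessments, and section 2.3 tells participants not to reveal their group. Bias is therefore not the main argument.

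Fourth, flexibility is largely a labelling matter. Passive goniometry, described in the same section, is a partial proxy, so it would be too strong to say that nothing bears on flexibility.

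Fifth, photographs without the orthosis show only lasting correction. The device is meant to be worn through the day, so alignment during wear would remain unmeasured. This objection stands in full and has to be stated with the result.

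**Conclusion.** The concern holds in a limited form. The realignment step has no quantitative endpoint, and the method stated for it does not yield the mean differences or Cohen's d that section 2.7 promises. The pressure step is well measured, so the trial keeps a partial test of its mechanism.

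The damage is confined to one secondary outcome and to the explanation of the result. It touches neither the primary comparison nor the sample size. No loss of power can be calculated, because the documents give no distribution or expected change for any toe angle.

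The conclusion rests on two assumptions: that section 2.6.3 describes the method actually in use, and that the joint markings allow angles to be read. If the camera view has varied, the second holds less well. A measured angle is nonetheless the better choice, because the photographs and the blinded staff are already planned.

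**What to change.** 1. In section 2.6.3, replace the qualitative evaluation with toe angles measured from the marked photographs: for example, the hallux valgus angle and the metatarsophalangeal and interphalangeal angles of the deformed toes. State beforehand which toe supplies each participant's value. Also state how participants are handled whose only qualifying deformity is a metatarsal head prominence or a fat pad change.
2. Fix a standard camera position. Photograph without the orthosis in both arms. Have the already planned blinded researcher read the images by code, without knowing the visit.
3. In section 2.7, compare the 6-month angle between arms adjusted for the baseline angle, with a 95 % confidence interval. State that this tests lasting correction, not alignment during wear.
4. Either tie flexibility in Table 1 and the 2.6.3 heading to the passive goniometry already scheduled, or remove it, so that sections 2.5, 2.6 and 2.6.3 agree.

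The cost is measurement time on at most 120 photograph sets, with no added visit. Angles depend on a consistent view. Section 3.1 reports that recruitment is under way, so baselines already photographed may be less precise and cannot be retaken. The camera position should therefore be settled soon, and the reading rule fixed before any outcome is seen.
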